
In summary, rehabilitation programs can contribute to a reduction in physical, neurocognitive, and psychological restrictions, thereby stabilizing or even increasing patients' physical and mental performance after recovery from COVID-19. This is a prerequisite for maintaining the ability to work on a long-term basis after COVID-19, which is associated with economic costs. Considering the diverse and variable symptomatology, especially the associated physical limitations, social and occupational participation disorders are to be expected. However, there is currently no research focusing on the nature and extent of returning to work after COVID-19. Consequently, COVID-19 is associated with great challenges for the healthcare systems worldwide. In addition to acute patient treatment, long-term care of COVID-19 patients will be necessary after the acute phase due to illness-related impairments. However, based on the lack of longitudinal data and results, the sustainability of rehabilitation effects could not yet be confirmed. Indeed, since patients with severe to critical COVID-19 seem to benefit from rehabilitation soon after the acute phase of infection, rehabilitation programs are recommended for all hospitalized COVID-19 patients to avoid long-term adverse health outcomes (53, 60). However, inpatient rehabilitation programs should not only be offered directly after hospitalization and temporary discharge, but also weeks and months after the acute phase of COVID-19, depending on the existing symptoms of post-COVID (51). Together with the case control management of health services, rehabilitation should be provided to regain functionality in everyday and workday activities.

In this context, this study examines the following main research questions:

- What are the long-term outcomes of patients following OAC after undergoing an intensive rehabilitation program? Of particular interest are patients' physical capacity, psychological and cognitive well-being, and ability to work.- Are age, gender, previous diseases, and employment at the time of exposure, as well as comorbidities associated with long-term outcomes of OAC of patients' physical capacity, psychological and cognitive well-being, and ability to work?- Are physical capacity and psychological and/or cognitive well-being predictors for ability to work or return-to-work?

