To detect the outcomes over time, differences between 2 dependent samples (T1 and T2) will be analyzed. The minimal clinically important difference between two measurement time points is 30 meters for the 6-minute-walking-distance (88). According to experience from our own studies on physical performance in patients with occupational respiratory diseases, standard deviations between 80 and 100 m are to be expected (100, 101). Assuming a standard deviation of 100 m (due to heterogeneity of the sample) and an expected effect size of d = 0.3, 71 data sets are required with a power of 80% and significance level of 5%.

While a drop-out rate of 25% is expected during the study period of 21 months, a total sample size of at least 115 patients will be included.

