### Statistical Analysis

IBM SPSS Statistics Version 28 and AMOS Version 28 (IBM Corp., Armork, NY, USA) will be used for all statistical analyses.

First, to determine the existing outcomes of COVID-19 on physical capacity, psychological and cognitive well-being, and the ability to work at the beginning of inpatient rehabilitation (T1), the population will be descriptively characterized by all measured outcomes. Data from participants at the end of inpatient rehabilitation (T2) and at the follow-up time points (T3, T4) will be analyzed to further evaluate the long-term outcomes of patients with COVID-19 undergoing an intensive rehabilitation in terms of physical capacity, psychological and cognitive well-being, and the ability to work. Normal distribution and homoscedasticity of the sample will be realized using the paired *T*-test or Wilcoxon-test. Depending on the feasibility for the current population, group differences (e.g., age, gender, pre-existing conditions, comorbidities, current employment) in the long-term effects of COVID-19 on physical capacity, psychological and cognitive well-being, and the ability to work will be analyzed separately for the different time points (T1, T2, T3, T4) using different statistical methods as follows. Taking into account the number and size of groups, normal distribution and homoscedasticity of the sample, parametric or non-parametric statistical methods such as the *T*-test, Mann-Whitney *U*-test, ANOVA, or the Kruskal Wallis test will be used. To evaluate the associations between the different outcome measures of physical capacity, psychological and cognitive well-being, and ability to work, correlation analysis will be performed to measure the strength of the relationship between two variables, e.g., 6MGT and HADS-D or 6MGT and WAI. Depending on these results and current insights from the literature, multivariate and logistic regression analyses accounting for confounders such as age, gender, or comorbidities will be conducted to identify predictors or meditators of the long-term outcomes of COVID-19. For example, a logistic regression analysis will be used to examine the relationship between physical capacity, psychological and cognitive well-being and the dependent variable return to work 6 or 12 months after the start of inpatient rehabilitation. For all analyses, Bonferroni correction for multiple testing will be applied and statistical significance level will be set to *p* < 0.05. After inspecting the amount and pattern of missing data and outlier values, the most appropriate procedure for addressing both factors will be selected.

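### Unequal variances are a criterion for choosing rank tests in the group comparisons, but rank tests do not correct for them; no unequal-variance method is named

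*Protocol article*

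**What the plan says.** The second research question in the Introduction reads "Are age, gender, previous diseases, and employment at the time of exposure, as well as comorbidities associated with long-term outcomes of OAC". It concerns physical capacity, psychological and cognitive well-being and ability to work.

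The Statistical Analysis section plans subgroup comparisons for this, separately at each of T1 to T4: "Depending on the feasibility for the current population, group differences (e.g., age, gender, pre-existing conditions, comorbidities, current employment"). The rule for selecting the test is "Taking into account the number and size of groups, normal distribution and homoscedasticity of the sample, parametric or non-parametric statistical methods such as the". Four tests are then named; the first is the T-test and the last two are in "ANOVA, or the Kruskal Wallis test will be used", with the Mann-Whitney test between them. Homoscedasticity is therefore one of the stated grounds for going parametric or non-parametric. The form of the T-test (pooled or Welch) is not given, and no method for unequal variances is named.

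The same section adds "For all analyses, Bonferroni correction for multiple testing will be applied and statistical significance level will be set to" p < 0.05. It also plans multivariate and logistic regressions with adjustment for confounders, to identify predictors of long-term outcome.

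**The concern.** If heteroscedasticity is a reason to leave the T-test or ANOVA, and the alternatives offered are Mann-Whitney and Kruskal-Wallis, the switch does not address the problem that prompted it. Both rank tests obtain their null distribution by exchanging observations between groups. That is valid only if the groups share one distribution, spread included.

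With unequal group sizes, a difference in spread alone then moves the error rate away from 5%. If the smaller group is the more variable, too many group differences are declared although means and medians agree. If the larger group is the more variable, the test becomes conservative and real differences are missed. Factors such as comorbidity or employment could well split the cohort unevenly, and a rejection would be read as an association with outcome.

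**Working it through.** **The plan's own figures.** The article gives no calculation for the subgroup comparisons. The figure behind the total sample size does reproduce: for the regression with f² = 0.15, 5 predictors, alpha 5% and N = 92, the noncentrality is 0.15 × 92 = 13.8 with 5 and 86 degrees of freedom, and the power is 80.4%.

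**Inputs.** The number analysed is 115 × (1 − 0.25) = 86.25, so 86 (total and drop-out rate from Sample Size Calculation). Group splits, SD ratios, normal outcomes, equal means and a two-sided 5% level are assumptions.

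**Why Mann-Whitney goes wrong.** Let the smaller group have size m and SD s, and the larger group size n and SD l.

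- Variance of U that the test assumes: mn(m + n + 1)/12.
- True variance for normal data with equal means: mn[1/4 + (n − 1)a + (m − 1)b], where a = arcsin(s²/(s² + l²))/(2π) and b = arcsin(l²/(s² + l²))/(2π).
- With s = l, a = b = 1/12 and the two variances agree.
- If R is true variance over assumed variance, the rejection rate is about 2Φ(−1.96/√R).

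For m = 17, n = 69 the assumed bracket is 87/12 = 7.25.

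- *Smaller group has twice the SD.* a = arcsin(0.8)/(2π) = 0.1476 and b = arcsin(0.2)/(2π) = 0.0320. The true bracket is 0.25 + 68 × 0.1476 + 16 × 0.0320 = 10.80. R = 1.49, √R = 1.22, rejection about 10.8%.
- *Larger group has twice the SD.* a and b swap. The bracket is 0.25 + 68 × 0.0320 + 16 × 0.1476 = 4.79. R = 0.66, √R = 0.81, rejection about 1.6%.
- *Smaller group has 1.25 times the SD.* a = 0.1044 and b = 0.0638. The bracket is 8.37. R = 1.15, √R = 1.07, rejection about 6.8%.
- *43 vs 43, ratio 2.* The bracket is 0.25 + 42 × (0.1476 + 0.0320) = 7.79. R = 1.075, rejection about 5.9%.

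**Simulation, equal means, nominal 5%** (20,000 runs per row; Monte Carlo standard error about 0.15 to 0.2 points near rates of 5% to 10%):

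| Smaller / larger n | SD smaller / larger | Pooled T-test | Mann-Whitney | Welch |
|---|---|---|---|---|
| 20 / 66 | 100 / 80 | 8.3% | 6.6% | 5.1% |
| 20 / 66 | 100 / 50 | 15.9% | 10.0% | 4.9% |
| 10 / 76 | 100 / 50 | 23.4% | 11.9% | 4.8% |
| 20 / 66 | 50 / 100 | 0.6% | 1.8% | 5.0% |
| 43 / 43 | 50 / 100 | 5.1% | 5.9% | 5.0% |
| 10 / 10 | 50 / 100 | 5.2% | 4.9% | 4.8% |

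At 17/69 with ratio 2, simulation gives 18.0% (pooled), 10.9% (Mann-Whitney) and 5.1% (Welch), in line with the formula. At 9/77 with ratio 2, Mann-Whitney reaches 12.7%.

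**Three groups** (8,000 runs). With sizes 50/26/10 and SDs 50/75/100, ANOVA rejects in 16.0% and Kruskal-Wallis in 9.3%. With SDs 80/90/100 the rates are 7.6% and 5.7%. With sizes 29/29/28 and SDs 50/75/100 they are 5.8% and 5.4%.

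**Does Bonferroni remove it?** The size of the family is not stated. As an illustration, take 0.05/4 = 0.0125 for four time points. At 17/69 with ratio 2, Mann-Whitney rejects in 4.0% and Welch in 1.2%. The excess relative to the nominal level grows.

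**Power in the reverse case.** At 17/69 with SDs 50 (smaller) and 100 (larger) and a true difference of 60 m, Mann-Whitney has about 81% to 82% power and Welch about 93%.

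**The case against.** The other side has substance, and most of it limits the point.

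- **The rule is partly inferred.** Homoscedasticity is one consideration among several. Nothing says that unequal variances alone trigger a rank test. A reader might infer that the plan prescribes rank tests here or excludes Welch. It does neither: the list follows the words such as, and a Welch test is also a T-test. What stands is that a parametric/non-parametric choice is tied to homoscedasticity and only rank tests are offered on the non-parametric side.
- **Small subgroups are not the cause.** A reader might infer that they are, but 10 vs 10 at ratio 2 is at 4.9%. Imbalance combined with unequal spread is needed.
- **The documents show no unequal subgroup variances.** A reader might take "Assuming a standard deviation of 100 m (due to heterogeneity of the sample) and an expected effect size of d = 0.3" in Sample Size Calculation as evidence. That remark concerns the overall SD in the paired T1-T2 calculation, and so does "standard deviations between 80 and 100 m are to be expected". Neither supports a subgroup SD ratio, and neither bounds one.
- **The switch helps somewhat.** Mann-Whitney is less inflated than the pooled T-test (10.0% against 15.9% at 20/66, ratio 2). That is true, but Welch is at 4.9% in the same setting.
- **Association is not only a difference in means.** A difference in distribution is an association too, so a rank-test rejection is not wrong in itself. It is wrong only if read as a difference in level, which is why the reporting wording matters.
- **Some outcomes are bounded scores.** For the MoCA, for example, rank tests may remain the right choice. The fix allows for this.

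**Conclusion.** The point holds as a minor improvement. Tying the choice of rank tests to homoscedasticity does not do what it appears meant to do, and neither the rank tests nor the pooled T-test and ANOVA keep the 5% level when unequal spread meets unequal group sizes.

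At N = 86, under the assumed splits, Mann-Whitney is at about 7% for an SD ratio of 1.25 and 10% to 13% for a ratio of 2 when the smaller group is the more variable. It is at about 1.5% to 2% for a ratio of 2 when the larger group is, and near 5% for equal group sizes. These figures rest on normal outcomes, equal means and assumed splits and ratios, because the article gives no subgroup sizes or SDs.

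The stronger conclusion that the second research question will be answered wrongly is not supported. The subgroup tests depend on feasibility, adjusted regressions are planned for the same question, and the sample size rests on the regression and the paired comparison, not on these tests.

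**What to change.** In Statistical Analysis, drop homoscedasticity as a reason to move to rank tests. For approximately normal outcomes, name the Welch T-test for two groups and Welch ANOVA with Games-Howell comparisons for more than two, as the standard methods without a preliminary variance test. Keep Mann-Whitney and Kruskal-Wallis for clearly non-normal or ordinal outcomes, and report their results as differences in distribution, not in mean or median.

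This is a change of a sentence or two, and the Welch procedures are standard output in SPSS, the software the plan names. The price is some power when variances are in fact equal and groups are unbalanced: about 76% against 79% for the pooled T-test at 17/69, and 81% against 83% at 20/66, so 2 to 3 points.

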The literature search resulted in very few studies investigating effects of COVID-19 on work capacity. In a meta-analysis including studies of patients infected with various corona viruses (SARS-CoV, MERS-CoV, SARS-CoV-2), Rogers et al. (27) showed that 446 of 580 patients from a total of 6 studies returned to work after an average of 35.3 months (27). Moreover, the expert group led by Kiekens et al. (49) referred to problems in performing work activities due to COVID-19 and recommended addressing this during follow-up treatment (49). Due to remaining symptoms up to 6 months after acute COVID-19, 45.2% of patients had to decrease working hours while 22.3% were unable to work (20). In the context of resuming work following COVID-19, it should be noted that working in the health care sector during the corona pandemic may have affected the mental health of staff. Lai et al. (50) examined 1,257 healthcare professionals caring for COVID-19 patients in China. These persons showed an increase in symptoms of depression (50.4%), anxiety (44.6%), insomnia (34.0%), and distress (71.5%) (50). Since stress might be a trigger for worsening symptoms, 85% of the patients reported improvements of symptoms with physical and mental training (20).

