
#### Measurements to Assess Work Ability

Employment status and ability to work will be assessed using the following questionnaires: the Work Ability Index [WAI; (83)] as primary outcome in this area of the investigation, the Brief Scale for Measuring Subjective Prognosis of Gainful Employment [SPE-Scale; (84)], and the History of work ability and employment after acute COVID-19 [in comparison to DEGS; (71)] (see also Table 1). These questionnaires assess functional recovery in terms of work ability and employment (e.g., days from diagnosis to first partial/complete return to previous work, work interruptions due to sick leave) for the subsequent period up to 12 months after the start of inpatient rehabilitation. Additionally, physicians will record detailed information during medical anamnesis.

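### Return-to-work dates are collected, but the only return-to-work analysis named is a logistic model of status at 6 or 12 months; a time-to-event model should be added beside it

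*Protocol article*

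**What the plan says.** The third research question in the Introduction is: "Are physical capacity and psychological and/or cognitive well-being predictors for ability to work or return-to-work".

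Under Measurements to Assess Work Ability, the questionnaires are said to yield "days from diagnosis to first partial/complete return to previous work, work interruptions due to sick leave". The period covered is "for the subsequent period up to 12 months after the start of inpatient rehabilitation". The plan therefore collects a time to event, separates partial from complete return, and records later interruptions.

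Under Statistical Analysis, the single analysis named for this outcome begins "For example, a logistic regression analysis will be used to examine the relationship between physical capacity, psychological and cognitive well-being" and takes as its outcome "the dependent variable return to work 6 or 12 months after the start of inpatient rehabilitation". The regressions are to be adjusted, "accounting for confounders such as age, gender, or comorbidities". No time-to-event method is named. The text does not say whether partial or complete return counts, or at which visit the predictors are measured. The handling of missing data is to be chosen once its amount and pattern have been inspected.

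The Sample Size Calculation covers a cross-sectional linear regression and a paired T1–T2 comparison. It expects 25% drop-out from at least 115 patients and does not cover the return-to-work model.

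**The concern.** A binary status at 12 months treats a patient who returned in month 1 and one who returned in month 11 as the same. A patient who leaves the study in month 8, still off work, has eight months of known follow-up, yet has no 12-month status and contributes nothing to a complete-case logistic fit. Both kinds of information are already in the data the study plans to collect.

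Two details of the wording add to this. Naming 6 or 12 months leaves open whether there is one model or two, and which carries the conclusion. Partial and complete return are recorded separately, but the outcome does not say which is meant. At stake is how precisely, and how reproducibly, the third research question is answered in a cohort of modest size.

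**Working it through.** **The plan's own figures.** For linear regression with f² = 0.15, 5 predictors and alpha 5%, the noncentral F distribution (λ = 0.15 × N; df 5 and N − 6) gives power 0.804 at N = 92 and 0.799 at N = 91. The stated 92 is therefore reproduced. The total of 115 equals 92 × 1.25. No event count or power is stated for return to work, so there is no plan figure to reproduce for that model.

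**Patients with a 12-month status.** 115 × 0.75 = 86.25, about 86. About 29 are expected to leave earlier.

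**Information per model term.** The text names three predictor domains and three example confounders. Entering all six together is a reading of those examples, not a stated model. A logistic model is limited by the smaller outcome class, a Cox model by the number of returns. The article gives no return rate, so a range is assumed. For logistic regression:

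- 50% return: 86 × 0.5 = 43; 43 / 6 = 7.2 per term
- 30% or 70% return: 86 × 0.3 ≈ 26; 26 / 6 = 4.3 per term

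**Power, simulation A.** N = 115, with exponential return times and baseline hazard −ln(1 − p)/12 per month for return proportion p. There is one standardised predictor with an assumed hazard ratio of 1.4. A quarter of patients drop out uniformly over 12 months and are censored at drop-out. Tests are two-sided at 5%, with 2000 runs per rate. Cox is compared with complete-case logistic regression at 12 months.

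| Return by 12 months | Returns used by Cox (per 6 terms) | Smaller class, logistic (per 6 terms) | Power, logistic | Power, Cox | Gain |
|---|---|---|---|---|---|
| 30% | 31 (5.2) | 27 (4.4) | 0.38 | 0.48 | 10 points |
| 50% | 52 (8.6) | 43 (7.1) | 0.55 | 0.66 | 11 points |
| 70% | 72 (12.0) | 26 (4.4) | 0.61 | 0.78 | 17 points |

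The per-term columns come from the simulated mean counts, so they differ slightly from the hand calculation above.

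**Power, simulation B.** This is less favourable to Cox: no return is possible in the first 3 weeks (the minimum inpatient stay), and drop-outs are censored at their last attended visit.

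| Return by 12 months | Power, logistic | Power, Cox | Gain |
|---|---|---|---|
| 30% | 0.37 | 0.41 | 4 points |
| 50% | 0.54 | 0.63 | 9 points |
| 70% | 0.62 | 0.75 | 13 points |

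With 2000 runs, the simulation standard error of a power near 0.5 is √(0.25/2000) ≈ 0.011, so differences of a point or two should not be read closely.

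The direction is the same at all three rates in both settings. The gain is smallest when few return and largest when most do, because the logistic model is then limited by the few who have not returned.

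**The case against.** **The analysis is only an example in a condensed article.** This stands in part. The logistic model is illustrative, and a full analysis plan may name others. A reader might infer that the study has committed itself to logistic regression alone, but the text does not say so. It remains the only return-to-work analysis described, beside a stated collection of return times.

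**6 or 12 months may mean one model at each follow-up visit.** That reading is possible. The wording also allows a choice between them, so it needs one clarifying sentence.

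**Status at 12 months is a legitimate outcome.** This stands. It reflects relapse into sick leave, which time to first return cannot. The Cox model should therefore be added and should not replace the logistic model.

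**Drop-outs are not necessarily lost.** This stands. Missing-data handling is deferred, so the loss applies to a complete-case fit and is not a stated feature of the plan.

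**The simulations favour Cox.** This stands as to size. Return times are generated under proportional hazards, all 115 patients are treated as at risk, and alpha is not reduced, although the article says "Bonferroni correction for multiple testing will be applied and statistical significance level will be set to" 0.05. The gain shrank but persisted in the less favourable setting.

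**Stronger readings that the article does not support.** The Introduction cites "446 of 580 patients from a total of 6 studies returned to work after an average of 35.3 months". That is 446/580 = 76.9%, and it is tempting to use it as the 12-month return rate, which would make the gain look larger. The figure pools several coronaviruses over a horizon about three times as long, so it is not used here. A reader might also suspect that predictors measured at T3 or T4 will enter the model and reflect being back at work. The article does not say so; it only leaves their timing open. Nor can sparse events be blamed on logistic regression alone: at 30% return the Cox model too has only about 5 returns per term.

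**Conclusion.** The point holds as a worthwhile, low-cost improvement. Return times are collected, yet the only return-to-work analysis named discards them and leaves both the time point and the type of return unsettled. Adding a Cox model would raise power by roughly 4 to 17 percentage points. That range rests on an assumed 30 to 70% return at 12 months, an assumed hazard ratio of 1.4 per standard deviation, proportional hazards, 25% drop-out, all 115 patients at risk, and a single predictor tested at an unadjusted 5%.

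The gain does not make the question well powered throughout. At 30% return both models stay below 0.50, and both have few events per term if six terms are entered. The logistic analysis is less efficient; it is not wrong.

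**What to change.** Add to Statistical Analysis, or to the analysis plan if one exists:

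- A Cox model for time from T1 to first complete return to work, among patients not working at T1, censored at last contact.
- Predictors measured at T1, with a T2 landmark analysis as sensitivity.
- The derivation of time from T1, since the recorded days run from diagnosis, and a note that return is not possible during the inpatient stay.
- The 12-month logistic model kept alongside, with partial or complete return specified, and a statement whether 6 months is a separate secondary model.

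The cost is wording only; no new data are needed. The drawbacks are a proportional-hazards check, a derived time origin, fewer patients if some already work at T1 (a number the article does not give), and a separate description of relapses after first return.

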#### Neurocognitive Measurements

##### Montreal Cognitive Assessment

Cognitive performance will be assessed using the MoCA as the primary outcome in this area of the investigation. The MoCa is a short screening tool to identify cognitive impairments in patients, i.e., in memory, attention, or executive functions. Following the recommendations by Nasreddine et al. (65), participants who reach a MoCA score between 30 and 26 points will be classified as cognitively healthy, whereas individuals with a MoCA score of 25 or lower will be considered cognitively impaired (65). To avoid learning effects, different versions of the MoCA will be implemented at different measurements points: Version 1 at T1, Version 2 at T2, Version 3 at T3, and again Version 1 at T4.

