##### 6-Minute Walk Test

The 6MWT, as the primary outcome in this area of the investigation, was chosen to assess functional exercise capacity. This test requires a walkway that is at least a 30m long. The walking course will be marked every 2 m. A cone will be placed on the ground to mark the turning points. The test coordinator will use a stopwatch to inform the participant when 6 min are over. Before starting the test, the participant has to sit on a chair close to the course for at least 10 min. The participant will be instructed to avoid talking while walking (87, 88). The outcome measure of the 6MWT is the distance in meters covered by the participant within 6 min. The 6MWT will be combined with a blood-gas analysis (Cobas b221, Roche Diagnostics intern., Rotkreuz, Switzerland) to provide information about the gas distribution of oxygen and carbon dioxide, the pH level, and the acid-base balance (89).

Finally, gait velocity of the first 10 meters of the 6MWT will be recorded to assess functional mobility, gait, and vestibular functions. The test coordinator will measure the time the participant requires to walk 10 meters, so that the velocity in seconds per meter can be calculated (90). Gait abnormalities will also be observed.

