### Sample Size Calculation

The sample size is calculated using G^*^Power 3.1.9.4 (University of Kiel) for the expected results of physical performance (6MWT) and mental well-being (depression). While 6MWT is a standardized measurement to assess physical capacity in patients with chronic disease during rehabilitation, e.g., COPD, (87–89) it was used as the primary outcome of physical performance for sample size calculation. 6MWT was also conducted in the first inpatient rehabilitation studies with patients with COVID-19 and showed good feasibility (31, 55). Multiple regression analyses assess the baseline situation of patients after acute COVID-19 with regard to physical resilience or mental health at the beginning of the inpatient rehabilitation. Due to the novelty of the disease, there are no representative comparative values for associations between COVID-19 and physical resilience and mental health. Therefore, the calculation of sample size in the cross-sectional analysis refers to the generic effect size measure *f*^2^. According to Cohen (97), a mean effect size of *f*^2^ = 0.15 will be used to calculate the sample size. Results from studies on correlations in patients with pneumological diseases (e.g., COPD) are used to justify this selected effect size in more detail. The study by Zeng et al. (98) identified age, severity of disease, and quality of life as significant predictors for physical performance measured by 6-minute-walking-distance in patients with COPD with a medium effect size of *f*^2^ = 0.21. In a regression model, von Leupoldt et al. (99) showed that depression is one out of 6 predictors (e.g., age, gender, forced expiratory volume in 1 s) for the completed 6MWT in COPD-patients in outpatient rehabilitation with a small effect size of *f*^2^ = 0.06 (71). Due to the heterogeneity of study results, a medium effect size of *f*^2^ = 0.15 can be assumed for the calculation of sample size to present associations between physical performance and mental health. With a planned power of 80% and significance level of 5%, 92 data sets are required, considering up to 5 potential predictors (e.g., pulmonary function values, blood gas values, age).

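### Both sample sizes give 80% power at an uncorrected 5% level, but the analysis section applies Bonferroni to every analysis, so the stated power does not belong to the planned tests

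*Protocol article*

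**What the plan says.** The Sample Size Calculation section of the protocol article makes two calculations.

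- **Multiple regression at the start of rehabilitation (T1).** A medium effect, f² = 0.15, "can be assumed for the calculation of sample size to present associations between physical performance and mental health". The result is: "With a planned power of 80% and significance level of 5%, 92 data sets are required, considering up to 5 potential predictors".
- **Paired comparison of 6MWT between T1 and T2.** A 30 m difference with a standard deviation of 100 m leads to "an expected effect size of d = 0.3, 71 data sets are required with a power of 80% and significance level of 5"%.

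The total is set at no fewer than 115 patients, with 25% drop-out expected over the 21-month study period.

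The Statistical Analysis section then sets the multiplicity rule: "For all analyses, Bonferroni correction for multiple testing will be applied and statistical significance level will be set to" p < 0.05. It does not say how many tests are counted, does not define a family, and does not exempt the two tests used for sizing.

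Three outcomes are each called primary in their own area:

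- **MoCA:** "Cognitive performance will be assessed using the MoCA as the primary outcome in this area of the investigation".
- **6MWT:** "The 6MWT, as the primary outcome in this area of the investigation, was chosen to assess functional exercise capacity".
- **WAI:** named in the Measurements to Assess Work Ability section "as primary outcome in this area of the investigation, the Brief Scale".

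The analysis section also plans group comparisons at each of the four time points, correlations between outcomes, and regression models.

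**The concern.** Power is a property of a test at a given significance level. If the level is divided by the number of tests, power at a fixed sample size falls. Here the sample size is justified at the full 5%, while the analysis rule says a smaller, unspecified level will be used throughout. The two statements cannot both describe the same test.

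Two things are at stake. First, the published power figure would be wrong for the analysis that is run. Second, because the number of tests is open, the threshold that a 6MWT change or a regression result must meet is also open. The same data could be called significant or not depending on how the tests are counted.

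**Working it through.** **Inputs from the Sample Size Calculation section.** Regression: f² = 0.15, 5 predictors, alpha 0.05, power 0.80, N = 92. Paired test: difference 30 m, SD 100 m, so d = 30/100 = 0.3; alpha 0.05, sidedness not stated, power 0.80, N = 71. Total 115; drop-out 25%, which leaves 115 × 0.75 = 86.25, taken as 86.

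**Assumed input.** The number of tests m is not in the article. A range is shown, with alpha = 0.05/m. The value m = 3 stands for one test per named area primary (MoCA, 6MWT, WAI).

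**Formulas.**
- Regression: overall test that R² = 0. Power = P(F′ > F crit), where F′ is noncentral F with 5 and N − 6 degrees of freedom and noncentrality f² × N.
- Paired test: noncentral t with N − 1 degrees of freedom and noncentrality d × √N.

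**Step 1: reproduce the stated figures.**
- Regression, alpha 0.05, N = 92: noncentrality 0.15 × 92 = 13.8, power 80.4%. The smallest N reaching 80% is 92, as stated.
- Paired, N = 71: noncentrality 0.3 × √71 = 2.53. One-sided at 0.05, power is 80.5% and the smallest N is 71, as stated. Two-sided at 0.05, power is 70.3% and 90 data sets are needed.

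So both stated figures use an undivided 5%, and the 71 is also one-sided.

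**Step 2: power at the stated sizes under Bonferroni.**

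| m | alpha | Regression, N = 92 | Paired one-sided, N = 71 | Paired two-sided, N = 71 |
|---|---|---|---|---|
| 1 | 0.05 | 80.4% | 80.5% | 70.3% |
| 2 | 0.025 | 71.3% | 70.3% | 59.5% |
| 3 | 0.0167 | 65.7% | 64.0% | 53.3% |

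**Step 3: power at the numbers that may be available.**

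| m | Regression, 115 | Paired two-sided, 115 | Regression, 86 | Paired two-sided, 86 |
|---|---|---|---|---|
| 1 | 89.9% | 89.1% | 77.0% | 78.5% |
| 2 | 83.7% | 82.6% | 67.2% | 69.1% |
| 3 | 79.6% | 78.3% | 61.3% | 63.3% |
| 12 | 63.5% | 61.6% | 42.0% | 44.0% |

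At 86 data sets power is already below 80% with no correction (m = 1). That part of the shortfall comes from the drop-out calculation: 115 = 92 × 1.25, whereas 92/(1 − 0.25) rounds up to 123. It is a separate matter and should not be charged to Bonferroni.

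**Step 4: data sets needed for 80% power at m = 3, before drop-out.** Regression 116; paired two-sided 120; paired one-sided 101.

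**The case against.** **The powered analyses come early.** The regression uses T1 data, and the paired test spans one inpatient stay of at least 3 weeks. The 25% drop-out is stated for the whole 21 months, so close to 115 data sets could be available for both. At 115, two tests keep power above 80%, and three leave the regression at essentially 80%. A one-sided paired test, the version that yields 71, keeps 85.5% at m = 3 and 82.6% at m = 4. This stands, and it limits the practical loss. It does not rescue the stated figures: the margin between 92 and 115 was added for drop-out, and no one-sided test is announced.

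**The 6MWT assumption is conservative.** The article expects an SD of 80 to 100 m and uses 100. At 80 m, d = 30/80 = 0.375, and two-sided power at m = 3 is 84.7% even with 86 data sets. This also stands, but it does not help the regression.

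**The family may be narrow and may be defined elsewhere.** Bonferroni could be meant within each set of repeated comparisons, and an article commonly leaves such detail to a fuller plan. That is why no single power figure can be given. The conflict itself remains, because the article fixes both statements and exempts nothing.

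**A stronger reading is tempting.** A reader might infer that the correction leaves the study unable to confirm the effects it was sized for, so that a real 30 m gain would be expected to come out non-significant. The documents do not support that. An expected non-significant result needs power below 50%. With 115 data sets, even twelve tests leave about 62% to 64%. Only a very large family, counting every outcome and time point, would support the inference, and the article does not define one.

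**Conclusion.** The inconsistency is real. The 80% power stated for 92 and 71 data sets holds only at an uncorrected 5% level, and the analysis section says that level will not be used. For any family of two or more tests, power at those sizes is below 80% under the article's own planning values: at most 71% for two tests and 66% for three.

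The loss in the study as run cannot be fixed to one number. It depends on the family size, which is assumed here, on how many of the 115 patients contribute at T1 and T2, and on sidedness and the SD. With a small family and nearly complete data at T2, it is modest. Because this is an observational cohort with largely descriptive aims, and an over-strict correction does not raise the false-positive rate, the point is should-fix.

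**What to change.** - Define one small confirmatory family that includes the T1–T2 6MWT comparison and the T1 regression, and test it with Holm, which is never less powerful than Bonferroni. Alternatively, name these two as pre-specified tests exempt from the correction.
- Report all other outcomes, time points, group tests and correlations as exploratory, with unadjusted 95% confidence intervals.
- State the sidedness of the paired test and restate power at the alpha actually used. For a family of just these two tests, the first Holm step is 0.025. Power is then 83.7% (regression) and 82.6% (paired, two-sided) with 115 data sets, or 67.2% and 69.1% with 86. If both are exempted at 5%, the figures are 89.9% and 89.1% with 115, or 77.0% and 78.5% with 86.

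The cost is wording and a stated power that is less favourable in some scenarios. This change alone requires no extra enrolment.
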